##### Indications of Used Drugs and Contraindications

The pharmacist checks the indications of the drugs used according to the patient’s comorbidities. The pharmacist checks whether all comorbidities are treated according to evidence-based medicine and according to treatment procedures developed by local, national, or international authorities. The result of this step is the identification of missing drugs in the patient’s pharmacotherapy.

Furthermore, drugs whose use has no clear indication are identified. In older adult patients (≥65 years), the pharmacist also considers the use of potentially inappropriate drugs. The pharmacist follows the EU (7)-PIM list [55], which was designed for patients aged 65 years and older. The result of this step is the identification of drugs that do not have a clear indication or are inappropriate due to the patient’s age.

The pharmacist also checks whether the prescribed drug is appropriate for the specific patient.

Drugs that the patient should and should not take, drugs whose indications are not clearly known from the available data, and contraindicated drugs are recorded in the final evaluation of the patient’s pharmacotherapy, in cooperation with the attending physician; subsequently, the most appropriate procedure is proposed.

##### Drug Management

The pharmacists verify compliance with maximum recommended doses, considering patient-specific factors, and records any excess in the pharmacotherapy evaluation. They assess the suitability of dosage forms, administration practices (including infusion components, timing, and food interactions), and screen for potential drug interactions using LexiComp and other resources, documenting any clinically significant findings. All observations and recommendations are reviewed with the attending physician to determine the appropriate course of action.

##### Adverse Drug Reactions

If a newly manifested ADR not documented in the patient’s medical history is suspected, the pharmacist evaluates the degree of causality between the drugs used and the manifestations of the ADR, which is proven on the basis of laboratory parameters or the patient’s subjective complaint. The pharmacist reports suspicions of ADR to the State Institute of Drug Control via an electronic form available from [56].

ADRs are recorded in the final evaluation of the patient’s pharmacotherapy.

The individual DRP findings shall be entered in the form as an appropriate code according to the PCNE classification [10].

The result of the pharmacist’s intervention at patient admission is the completion of the MedRec form at admission and creation of an accurate list of medicines taken by the patient. All comments on pharmacotherapy with the proposed solutions are written in the form of a summary report and undergo consultation with the physician.

#### At Hospital Discharge

##### Current Condition at Patient Discharge

When discharging a patient, the attending physician evaluates the patient’s state of health and prepares a discharge report with complete information about the procedures that the patient underwent during hospitalization. The discharge report also includes the current results of the patient’s laboratory examinations, an overview of current pharmacotherapy, and recommendations to the patient’s general practitioner. The nurse explains the regimen measures in relation to his or her state of health to the patient and gives the patient medication for the 3 days following discharge.

##### MedRec by Pharmacists at Patient Discharge

The pharmacist performs MedRec when discharging a patient from the hospital, similar to the process at admission. When evaluating a patient’s pharmacotherapy on discharge from hospital, the BPMH obtained at the patient’s admission will be used as a source of information. The BPMH is then compared with the list of medicines that are recorded in the release report. The pharmacist will compare 2 lists of medicines, focusing on the identification of DRPs with special regard to the re-introduction of the chronic therapy the patient was taking before hospitalization. As part of this research, the pharmacist met with the patient during his or her discharge from the hospital and discussed with him or her the management of further pharmacotherapy. Pharmacists provided an understandable summary list of a patient’s medicines explaining the importance and the correct use of the medicine.

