## Introduction

### Background

Pharmaceutical care was first defined in 1990 by Hepler and Strand [1] as “the responsible provision of drug therapy for the purpose of achieving definite outcomes that improve a patient’s quality of life.” Worldwide, pharmaceutical care is currently considered a patient-centered approach, replacing the previous product orientation (dispensing medications) [2,3]. The pharmacist actively cooperates not only with the patient but also with health care professionals in health promotion, disease prevention, evaluation, monitoring, and adjustment and initiation of drug use in order to ensure an effective and safe drug regimen, achieve positive clinical results, and reduce the economic costs of care [2,4].

Currently, patient safety in health care delivery is at the forefront of interest worldwide [5,6]. Patient safety is the absence of preventable harm to a patient during the process of providing health care and reduction of the risk of unnecessary harm associated with health care to an acceptable minimum. Hospital pharmacists [4,7] can make a significant contribution to the safe, effective, and rational use of medicines by hospitalized patients, especially high-risk medication and look-alike and sound-alike medications, through their close surveillance as well as advising on the most appropriate use of medicines [7]. Identification of drug-related problems (DRPs) and proposal of solutions for DRPs by hospital pharmacists is a tool to ensure safe and effective pharmacotherapy for patients [8,9].

The Pharmaceutical Care Network Europe Association (PCNE) defines a DRP as a problem, event, or circumstance related to pharmacotherapy that affects or has the potential to affect a desired therapeutic effect [10]. An example is the arbitrary withdrawal of metformin by patients due to persistent diarrhea [11]. The PCNE has developed a classification system as a tool to accurately identify DRPs. The current version is V9.00 as of 2019 [10]. This classification tool is used throughout our study to ensure consistency in identifying and categorizing DRPs.

DRPs are generally all problems related to the use of a drug [10]. DRPs include adverse drug reactions (ADRs), an unintended reaction after medication administration [11-14], medication errors, and any phenomenon that may lead to improper use of a drug under the control of a health care professional or patient [15-17].

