### Primary Outcomes

The primary outcome is a change in the prevalence of DRPs at hospital admission versus hospital discharge.

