One of the recorded parameters is patient understanding. This is evaluated in 3 steps and scored as 0 or 1: The patient knows (1) or does not know (0) the name of the drug, the patient knows (1) or does not know (0) the indication of the drug, and the patient knows (1) or does not know (0) the dosage of the drug. The 3-point scale was based on previously published studies by Cline et al [52], Boonstra et al [53], and Marfo et al [54], who evaluated patients’ knowledge based on their understanding of the drug name, dosage, duration of treatment, indication, relationship of the drug to food, duration of therapy, or route of administration. If the patient was unable to attend the interview, other sources were used to obtain a medical history or to clarify conflicting information. Other resources should never be a substitute for a thorough conversation with the patient or family members.

Regarding verification and documentation of the BPMH, the BPMH list should be verified by more than one other source. Sources for the initial acquisition of an overview of pharmacotherapy are the admission report, the history of hospitalization, outpatient reports, HIS, and the course at admission.

According to the World Health Organization standard operating procedure, a retroactive MedRec model was used for our biomedical research. In a retroactive model, in accordance with the aforementioned method, the patient is admitted by a physician in cooperation with a nurse by default, and a drug course—a daily prescription of drugs for the patient – is created. In this case, the BPMH is determined after admission by a physician or nurse.

The result of the MedRec is a comparison of medicines prescribed to and actually used by patients (BMPH) with marked discrepancies.

During the process of obtaining the BPMH, the pharmacist informs patients to always share their doubts about the correct use of the medication with the medical staff.

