##### MedRev With Pharmaceutical Intervention at Patient Admission

The basis for patient therapy optimization is the acquisition of the BPMH and patient factors, such as the reason for hospitalization, current health status, comorbidities, height, weight, heart rate, blood pressure, and the results of examinations of biochemical and hematological parameters.

The detected BPMH is written in the case report form. It is then analyzed in the context of the patient’s overall health condition, and DRPs are identified. Each detected discrepancy is assigned an alphanumeric code according to the PCNE V9.00 classification. The patient’s personal data are anonymized.

Discrepancies in therapy should be consulted with the treating physician within 24 hours of admission.

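### Admission and discharge DRP counts are not fully like for like, so part of the primary paired reduction may reflect what could be counted at each time

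*Protocol article*

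**What the plan says.** Primary Outcomes states: "The primary outcome is a change in the prevalence of DRPs at hospital admission versus hospital discharge". Statistical Methods compares the number of DRPs at the two times with a paired Wilcoxon signed-rank test.

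**Admission.** The pharmacist builds a BPMH at the bedside, recording what the patient is really taking. MedRec by Pharmacists at Patient Admission gives the product of this step: "The result of the MedRec is a comparison of medicines prescribed to and actually used by patients (BMPH) with marked discrepancies". MedRev With Pharmaceutical Intervention at Patient Admission then says of the BPMH: "It is then analyzed in the context of the patient’s overall health condition, and DRPs are identified". It adds: "Each detected discrepancy is assigned an alphanumeric code according to the PCNE V9.00 classification".

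**Discharge.** MedRec by Pharmacists at Patient Discharge says that "the BPMH obtained at the patient’s admission will be used as a source of information". It continues: "The BPMH is then compared with the list of medicines that are recorded in the release report". The comparison is described as "focusing on the identification of DRPs with special regard to the re-introduction of the chronic therapy the patient was taking before hospitalization". No new history of use is described. The pharmacist does meet the patient, but the stated purpose is to discuss further treatment and explain the medicines.

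The same discharge sections say that reconciliation and review follow the admission pattern, and Background says that one PCNE classification is used throughout. Limitations of the Study mentions subjectivity in DRP assessment and the absence of a control group, but not this difference.

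**The concern.** A paired before-after contrast can be read as an effect only if the same quantity is measured twice. Here one class of DRP depends on knowing how the patient uses medicines. Background offers such a case when it illustrates the DRP definition: "An example is the arbitrary withdrawal of metformin by patients due to persistent diarrhea". At admission that information is collected directly. At discharge the use information is the admission record, and the new regimen has not been taken at home, so fresh use problems have little chance of being recorded.

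If such problems drop out of the discharge count because they are hard to see, the count falls even when care has changed nothing. The study has one arm, so no concurrent group would show the same fall and expose it.

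**Working it through.** **1. The two assessments side by side**

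| | Admission | Discharge |
|---|---|---|
| History of actual use | Taken fresh (BPMH) | Admission BPMH reused |
| List set against it | Prescribed medicines | Release-report list |
| Regimen already used by the patient | Yes | Not yet, as a discharge regimen |
| Review checks (duplication, indication, dose, interactions, adverse reactions) | Described in full | Repeated by reference to admission |
| Particular focus | None of this kind | Re-introduction of chronic therapy |

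The BPMH is common to both columns, and so are the review checks. What differs is the list being checked and whether use is newly ascertained.

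**2. The plan's own figure**

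Study Sample Size gives 94 patients for effect size 0.3, 80% power and alpha 0.05. A noncentral t calculation with asymptotic relative efficiency 3/π (normal parent, two-sided) reproduces it. The effective n is 94 × 0.955 = 89.8, the noncentrality is 0.3 × √89.8 = 2.84, and the power is 0.803. At 100 patients, the number reported as reached, power is 0.827. This point leaves those figures unchanged.

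**3. Illustrative model (assumptions, not document figures)**

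- n = 100, from Study Initiation and Recruitment.
- Admission count A is Poisson with mean m = 1.3 or 1.7. These are the per-patient averages that Comparison With Prior Work reports from two cited studies.
- No true change: half of A persists and is replaced by new DRPs with mean 0.5m.
- A share q of DRPs present at discharge cannot be seen there. Extra discharge flags are added with mean r·m.

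Expected difference: m − (1 − q)m − r·m = (q − r)m.

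Variance of the difference: m + (1 − q + r)m − 2 × 0.5(1 − q)m = (1 + r)m.

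Apparent standardised change: d = (q − r)·√(m/(1 + r)).

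The test is a two-sided Wilcoxon at 0.05, with 1,500 simulated trials per setting. Each cell gives m = 1.3 / m = 1.7.

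| q | r | d, formula | d, simulated | Rejection |
|---|---|---|---|---|
| 0 | 0 | 0 / 0 | −0.002 / 0.000 | 5.7% / 5.0% |
| 5% | 0 | 0.057 / 0.065 | 0.062 / 0.067 | 8.5% / 10.8% |
| 10% | 0 | 0.114 / 0.130 | 0.113 / 0.132 | 19.9% / 26.8% |
| 20% | 0 | 0.228 / 0.261 | 0.230 / 0.266 | 61.4% / 72.1% |
| 30% | 0 | 0.342 / 0.391 | 0.344 / 0.392 | 92.6% / 97.7% |
| 0 | 20% | −0.208 / −0.238 | −0.209 / −0.239 | 54.0% / 64.6% (towards an increase) |
| 20% | 20% | 0 / 0 | 0.005 / 0.001 | 4.8% / 4.2% |

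**4. Against the planned effect**

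With r = 0, the artefact alone equals the planned effect of 0.3 when q = 0.3/√m. That is 0.3/1.140 = 26% for m = 1.3 and 0.3/1.304 = 23% for m = 1.7.

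**The case against.** The strongest reply is that the two assessments share more than they differ.

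- The BPMH is one side of both comparisons, and an admission-discharge design must change the list being checked.
- Review is repeated at discharge with the same checks under one classification.
- Some use problems can still surface. If the release report lists a drug that the BPMH shows the patient had stopped, the discharge comparison exposes it. If the drug is left off, the check for untreated comorbidities may flag it. The pharmacist also meets the patient.

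All of this stands. It means that only part of the count is affected. A reader might infer that DRPs are counted against wholly different references; the shared BPMH rules that out. But the statement that discharge resembles admission does not remove the difference, because the same section goes on to specify a comparison without a new use history.

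A reader might also infer that changes made on the pharmacist's advice are coded as new DRPs at discharge, since they depart from the admission BPMH. The article does not say so. The sentence on coding every discrepancy is in the admission section. Background separates intentional from unintentional DRPs and directs attention to the latter, and recommendations are documented in writing. A detailed rule for intended changes may be in the full protocol, the analysis plan or the procedure scheme, none of which is shown.

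Finally, the shares q and r are assumed. That is correct, and the table is only an illustration.

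**Conclusion.** The concern holds in a limited form. The article does not show the admission and discharge counts to be fully like for like: use-related DRPs can be recorded more readily at admission, which leans the uncontrolled paired contrast towards an apparent reduction.

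The size cannot be computed from the document. Under the stated assumptions, a hidden share of 5% already raises two-sided rejection to about 9-11%; 10% gives 20-27% and 20% gives 61-72%. Extra discharge flags would act in the opposite direction, and at 20% each the two cancel.

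A reader might go further and conclude that an observed reduction is an artefact. The document does not support that, because neither the share of affected DRPs nor the net direction is known. The supported statement is that part of the reduction may be an artefact, and that the planned analysis alone cannot tell.

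**What to change.** Add a like-for-like paired analysis using the PCNE codes already recorded.

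- Restrict it to DRP categories that can be assessed at both times, that is, prescribing or list-related ones. Apply the same inclusion rule at admission and discharge.
- Do not count documented intended changes as DRPs.
- Report patient-use DRPs descriptively at admission.
- Present this result beside the all-DRP comparison, and conclude that DRPs fell only if the two agree.
- Add the difference in ascertainment to Limitations of the Study.

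The primary outcome itself should stay as defined. Analysis and Reporting Milestones dates the primary analysis to January 2024, so the added analysis must be labelled post hoc.

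**Cost.** This is mainly re-tabulation of DRPs already in the case report form, with the recorded acceptance of recommendations. The article does not say whether changes initiated by physicians are also captured there, so some may need checking in the medical record. The restricted count is smaller and the analysis has less power.

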##### MedRev With Pharmaceutical Intervention at Patient Discharge

The pharmacist analyzes the pharmacotherapy in the context of the patient’s state of health and the results of laboratory tests, similar to the patient’s admission, as described in the previous sections. Detected DRPs are then consulted with the treating physician and recorded in the case report form.

The result of the pharmacist’s intervention at discharge is the completion of the MedRec form for discharge and the documentation of all comments on pharmacotherapy in the form of a summary report. Discrepancies and comments are consulted with the physician.

The complete scheme of the procedure can be seen in Figure 1.

**Figure 1 figure1:**
[figure not shown]
Procedure scheme.

### Ethical Considerations

#### Human Subject Ethics Review Approvals

The study was approved by the Ethics Committee of the National Institute of Cardiovascular Diseases (approval number 1625/21; May 26, 2021) and registered on ClinicalTrials.gov (trial registration number NCT04930302; June 16, 2021). All research procedures adhered to the ethical standards of the institutional and national research committees and were conducted in accordance with the 1964 Helsinki Declaration and its later amendments or comparable guidelines.

#### Informed Consent

Written informed consent was obtained from all participants before any research-related activities were initiated. The consent form, approved by the Ethics Committee, was provided in Slovak to ensure participants’ understanding. By signing the consent form, participants consented to the publication and presentation of their pseudonymized data.

#### Privacy and Confidentiality

Patients’ personal data were anonymized to ensure confidentiality. The Participant Identification Sheet was securely stored at the study center, alongside other documentation. Anonymized data were entered into the case report form in the MIA DMS online database, which operates within Europe.

#### Compensation Details

No compensation was provided to participants for their involvement in this study.

## Results

This protocol outlines the planned study design and anticipated timeline for the PHAROS trial, aimed at evaluating the impact of pharmacist-led interventions on DRPs in patients undergoing vascular surgery. The key stages of the trial and their anticipated completion dates are described in the following sections.

### Study Initiation and Recruitment

Patient recruitment began in September 2021 and was completed in **A**ugust 2022. The target sample size of 100 patients was reached.

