**Methods:**

This prospective, uncontrolled study was conducted over 1 year in the Vascular Surgery Department at the National Institute of Cardiovascular Diseases in Bratislava, Slovakia. The study included adult patients with carotid artery disease or lower extremity artery disease who were on 3 or more medications, with an estimated sample size of approximately 100 patients. The primary intervention involved 3 key changes in practice: medication reconciliation at both admission and discharge, where hospital pharmacists review and verify medication lists; medication review to identify and address drug-related problems; and patient education at discharge. Pharmacist-proposed interventions were documented and communicated to the physician for treatment adjustments. The primary outcome is the change in drug-related problem prevalence from hospital admission to discharge. Secondary outcomes include the acceptance rate of pharmacist recommendations and patient understanding of pharmacotherapy. Data collection involved documenting the number, type, and frequency of drug-related problems; the anatomical therapeutic chemical classification of medications associated with drug-related problems; and patients’ social, demographic, and clinical characteristics, with a focus on factors related to drug-related problems, comorbidities, and medication use. Data analysis will use the paired Wilcoxon signed-rank test to compare the prevalence of drug-related problems and medication counts between admission and discharge. Continuous variables will be presented as means (SDs), while categorical variables will be reported as counts and percentages. Patient understanding of pharmacotherapy will be evaluated using a 3-point scale, classifying understanding as good (2-3 points per medication), modest (1-2 points), or poor (0-1 point).

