### Trial Hypotheses

The null hypothesis is that pharmaceutical care provided at hospital admission and hospital discharge does not reduce the prevalence of DRPs in patients with carotid artery disease or lower extremity artery disease hospitalized in the Department of Vascular Surgery.

The alternative hypothesis is that pharmaceutical care provided at hospital admission and hospital discharge reduces the prevalence of DRPs in patients with carotid artery disease or lower extremity artery disease hospitalized in the Department of Vascular Surgery.

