### Study Sample Size

To calculate the sample size, we aimed to accept a type I error rate with a *P* value ≤.05. The study seeks to achieve 80% power to detect a small effect size of 0.3 using the Wilcoxon signed-rank test. Based on these assumptions, the required sample size was calculated as 94 patients. To account for potential dropouts, the sample size was increased to 120 patients. The sample size calculation was performed using G*Power software version 3.1 [50]. Similar studies published in this field have comparable sample sizes [51].

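### The article gives two sample size targets, 120 and 100, without reconciling them; if 100 is the number enrolled, the dropout margin shrinks from 26 patients to 6

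*Protocol article*

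**What the plan says.** The protocol article gives the sample size in three places.

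- **Study Sample Size.** The design basis is "The study seeks to achieve 80% power to detect a small effect size of 0.3 using the Wilcoxon signed-rank test", and "the required sample size was calculated as 94 patients". The next step is "To account for potential dropouts, the sample size was increased to 120 patients". No dropout rate is given.
- **Abstract, Methods.** The study is described "with an estimated sample size of approximately 100 patients".
- **Results, Study Initiation and Recruitment.** After the recruitment dates (September 2021 to August 2022) the text reads "The target sample size of 100 patients was reached".

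Primary Outcomes and Statistical Methods make the main comparison a paired one: drug-related problems at admission against discharge, by the Wilcoxon signed-rank test. A patient contributes only with both assessments.

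**The concern.** All three statements are current text, and they cannot all describe the same planned number. A sample size raised to 120 is not a target of 100. Condensing a protocol into an article does not explain this, because the article prints both figures.

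What is at stake is the protection the plan built around its power. The increase to 120 exists so that 94 patients remain for the paired test after losses. If recruitment closed at 100 enrolled, most of that protection is gone, yet the reader is told without qualification that the target was met. A reader cannot tell from the article which number the stated 80% power rests on.

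**Working it through.** **Inputs**

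- Significance level 0.05 (Study Sample Size: "we aimed to accept a type I error rate with a *P* value ≤.05").
- Power 80%, standardized effect d = 0.3, Wilcoxon signed-rank test (same section).
- Software: "The sample size calculation was performed using G*Power software version 3.1".
- Sidedness is not stated. The alternative in Trial Hypotheses is directional ("pharmaceutical care provided at hospital admission and hospital discharge reduces the prevalence of DRPs"), so both versions were tried.
- Parent distribution is not stated; several were tried.

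**Step 1: reproduce the 94.** Power uses the asymptotic relative efficiency (A.R.E.) method. For N pairs, take n = N × A.R.E., with A.R.E. = 3/π for a normal parent. Power comes from a noncentral t with n − 1 degrees of freedom and noncentrality 0.3 × √n.

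For N = 94, two-sided: n = 94 × 3/π = 89.8, noncentrality = 0.3 × √89.8 = 2.84, power = 80.3%. At N = 93 power is 79.85%, so 94 is the smallest N that reaches 80%. The plan's figure reproduces exactly.

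The other versions tried do not give 94. One-sided with a normal parent gives 74, and a two-sided paired t test gives 90. Two-sided logistic, Laplace and minimum-efficiency parents give 82, 60 and 104. Two-sided with a normal parent is therefore the inferred basis. A simulation of 10,000 trials with normal differences gave 80.6% at 94 pairs.

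**Step 2: margin for loss under each target**

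- Target 120: 120 − 94 = 26 patients; 26/120 = 21.7%.
- Target 100: 100 − 94 = 6 patients; 6/100 = 6%.

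**Step 3: power if 100 is the number enrolled.** Same formula, two-sided, normal parent. The loss rates are assumptions. The last column uses the approximation 0.3 × √(94/N).

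| Assumed loss | Complete pairs N | Power at d = 0.3 | Effect detectable at about 80% power |
|---|---|---|---|
| 0% | 100 | 82.7% | 0.29 |
| 5% | 95 | 80.7% | 0.30 |
| 6% | 94 | 80.3% | 0.30 |
| 10% | 90 | 78.5% | 0.31 |
| 15% | 85 | 76.1% | 0.32 |
| 20% | 80 | 73.5% | 0.33 |

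**Step 4: power if 100 is the number evaluable.** This is the first row: 82.7% (83.0% by simulation), above the planned 80%.

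**The case against.** The strongest defence is that 100 exceeds 94, so on the plan's own figures the power may be intact. The article does not say whether the 100 are enrolled or evaluable. If they are evaluable, the drop from 120 to 100 (20/120 = 16.7%) lies inside the plan's own allowance. Even if they are enrolled, both assessments fall within one planned hospital stay, with no follow-up after discharge to lose, so 94 complete pairs out of 100 is plausible. All of this stands, and it limits the point to an unreconciled target with a conditional consequence.

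Three stronger readings are tempting, and the document does not support them.

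- **Recruitment fell 20 short and the target was missed.** The recruitment heading makes enrolled the more natural reading of 100, but the text does not establish it. The abstract speaks only of an estimated size and does not say that anything was reached.
- **Power is about 72%.** That figure applies a 21.7% loss to 100 enrolled (78 pairs, 72.4%). The 21.7% is only back-calculated from 94/120. A 20% allowance gives 94/0.8 = 117.5, or 118, so 120 could be a rounded figure. An allowance is also not a forecast of loss.
- **Because Statistical Methods calls the differences non-normal, 94 is too few.** The minimum-efficiency case needs 104, but logistic and Laplace parents need 82 and 60. Non-normality alone does not settle the direction.

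What the defence does not remove is that 120 and 100 are both printed as the planned size, with no explanation.

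**Conclusion.** The point holds as an internal contradiction in a core design figure. The calculation of 94 is correct under a two-sided test at 0.05, d = 0.3 and a normal parent; the error lies in the conflicting targets.

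The consequence depends on what the 100 counts. If enrolled, the margin for incomplete pairs is 6 patients instead of 26, and 80% power is kept only with 94 or more complete pairs; over an assumed loss of 0% to 20%, power runs from 82.7% to 73.5%. If evaluable, power is adequate. A reader might infer that the trial is underpowered, but the document does not show that. Had the test been one-sided, 78 pairs would still give 82.1%, although the plan's 94 does not reproduce on that basis.

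Correction is needed under either reading, because at least one of the three statements is wrong or unexplained as printed.

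**What to change.** - State the sample size the same way in the abstract, Study Sample Size, and Study Initiation and Recruitment: 94 evaluable admission-discharge pairs required, 120 patients planned.
- Say whether 100 is the number enrolled or the number evaluable.
- Explain the departure from 120. If 100 is the enrolled count, withdraw the statement that the target was reached.
- Report the actual number of complete pairs, and restate the power or the detectable effect for that number.

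The cost is wording only. Recruitment ended in August 2022 and the primary analysis was completed in January 2024, so these counts should already be available. No patients, tests or endpoints change. If 100 were enrolled and fewer than 94 pairs are complete, the stated power becomes less favourable.
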